## Abstract

**Background:**

Peritoneal dialysis (PD) is the preferred dialysis modality in children. Its major drawback is the limited technique survival due to infections and progressive ultrafiltration failure. Conventional PD solutions exert marked acute and chronic toxicity to local tissues. Prolonged exposure is associated with severe histopathological alterations including vasculopathy, neoangiogenesis, submesothelial fibrosis and a gradual loss of the mesothelial cell layer. Recently, more biocompatible PD solutions containing reduced amounts of toxic glucose degradation products (GDPs) and buffered at neutral pH have been introduced into clinical practice. These solutions contain lactate, bicarbonate or a combination of both as buffer substance. Increasing evidence from clinical trials in adults and children suggests that the new PD fluids may allow for better long-term preservation of peritoneal morphology and function. However, the relative importance of the buffer in neutral-pH, low-GDP fluids is still unclear. In vitro, lactate is cytotoxic and vasoactive at the concentrations used in PD fluids. The BIOKID trial is designed to clarify the clinical significance of the buffer choice in biocompatible PD fluids.

**Methods/design:**

The objective of the study is to test the hypothesis that bicarbonate based PD solutions may allow for a better preservation of peritoneal transport characteristics in children than solutions containing lactate buffer. Secondary objectives are to assess any impact of the buffer system on acid-base status, peritoneal tissue integrity and the incidence and severity of peritonitis.

After a run-in period of 2 months during which a targeted cohort of 60 patients is treated with a conventional, lactate buffered, acidic, GDP containing PD fluid, patients will be stratified according to residual renal function and type of phosphate binding medication and randomized to receive either the lactate-containing Balance solution or the bicarbonate-buffered Bicavera^® ^solution for a period of 10 months. Patients will be monitored by monthly physical and laboratory examinations. Peritoneal equilibration tests, 24-h dialysate and urine collections will be performed 4 times. Peritoneal biopsies will be obtained on occasion of intraabdominal surgery. Changes in small solute transport rates, markers of peritoneal tissue turnover in the effluent, acid-base status and peritonitis rates and severity will be analyzed.

## Background

Peritoneal dialysis (PD) is the preferred dialysis modality in children. Advantages of PD over hemodialysis relevant to pediatric patients include its compatibility with a normal lifestyle and full psychosocial integration, the continuous mode of blood purification without dysequilibrium conditions, the absence of vascular access issues and the avoidance of puncture pain. However, the major drawback of PD is its limited technique survival. Almost fifty percent of adult as well as pediatric PD patients must switch to hemodialysis within 4 to 5 years of treatment [1,2]. While the incidence of PD failure due to infectious complications is steadily decreasing, loss of ultrafiltration due to degenerative changes of the peritoneal tissue is becoming the leading cause of non-elective termination of PD [1]. Histopathological alterations induced by exposure to PD solutions include a severe vasculopathy, neoangiogenesis, submesothelial fibrosis and a progressive loss of the mesothelial cell layer [3-5]. Acute and chronic toxicity of standard PD fluids to mesothelial cells, affecting cell turnover and the pattern of growth factor and cytokine release, is considered a key mechanism underlying the progressive transformation of the peritoneum. Conventional PD fluids contain large doses of glucose, are lactate-buffered at acidic pH and contaminated with toxic glucose degradation products (GDP) formed during heat sterilization. Low pH, lactate and hyperosmolar glucose independently impair mesothelial cell functions [6-9]. GDPs impair the viability and functional integrity of mesothelial cells upon extended exposure [10], and stimulate VEGF and TGF-β release by mesothelial cells [11,12].

In recent years, a new generation of more biocompatible PD fluids has been introduced into clinical practice. The separation of alkaline and acidic fluid compartments in pluri-chamber bags permits to sterilize glucose at very low pH with greatly reduced GDP formation and yet produce pH-neutral final dialysis solutions, using lactate and/or bicarbonate as a buffer. We recently compared the safety and efficacy of Bicavera^® ^(Fresenius), a purely bicarbonate-buffered biocompatible PD solution, with that of a conventional acidic, lactate buffered solution by a three-month crossover trial in children on automated PD [13]. We observed a marked increase of the mesothelial cell marker CA125 in the effluent during Bicavera^® ^treatment, which was readily reversible when patients returned to conventional solution. This effect was also observed with lactate- or lactate/bicarbonate-buffered biocompatible PD solutions [14,15], and is interpreted as a functional and/or numeric recovery of mesothelial cells exposed to these fluids. Moreover, in agreement with previous studies [7,16] we observed a trend towards increasing small solute permeability with the standard solution; this trend was absent when Bicavera^® ^was used. Two studies observed a slightly lower initial increase of the functional peritoneal surface area during a single PD dwell with pH-neutral compared to acidic solutions compatible with reduced peritoneal capillary recruitment; this trend was significant in one study [17-19]. Fischbach et al. also demonstrated lower intraperitoneal pressure and less inflow pain in children receiving a low-GDP, neutral-pH PD solution [19]. Finally, we noted a more effective compensation of metabolic acidosis with Bicavera^® ^than with lactate buffered conventional fluid despite identical content of base equivalents.

While these results are encouraging with respect to the long term preservation of the peritoneal membrane and strongly favour the primary use of low-GDP, neutral-pH biocompatible PD fluids, the relative importance of the buffer system is still unclear. In vitro data suggest that lactate per se may compromise local cell functions independently of pH by affecting the cellular redox state and reducing cellular energy sources [6,20-22]. By intravital microcopy of rat peritoneum, lactate-based neutral-pH PD solution caused mesenteric vasodilation whereas bicarbonate buffered PD fluid had no hemodynamic effects [23]. All previous clinical trials comparing conventional and biocompatible PD fluids were unsuitable by design to identify any role of the buffer for peritoneal tissue integrity, perfusion and the acute or chronic regulation of peritoneal solute transport, since the solutions tested differed not only by the buffer used, but also by pH and GDP content. To clarify the role of the buffer the BIOKID trial has been designed. Patients participating in this trial will be exposed to two solutions which are both pH neutral and of low GDP content, but contain either pure bicarbonate or pure lactate as buffer compound.

## Methods/design

### Objectives of the study

The European Pediatric Peritoneal Dialysis Study Group (EPPS) plans a prospective, randomized study with administration of pH neutral, low-GDP PD solutions containing either lactate or bicarbonate buffer over a period of 10 months.

The primary objective is to evaluate the effect of lactate vs. bicarbonate buffer on peritoneal transport capacity in children. The hypothesis to be tested is that bicarbonate based PD solutions may allow for a significantly better preservation of peritoneal transport characteristics (D/P_Crea_) in children compared to a solution containing lactate buffer. Secondary objectives will be to assess differential effects of lactate and bicarbonate buffered PD fluids on acid-base status, surrogate parameters of peritoneal biocompatibility and local and systemic carbonyl stress, peritoneal morphology, the incidence and severity of peritonitis, statural growth and nutritional status. Moreover, this study will be used to assess genetic determinants of the peritoneal transporter status and the evolution of peritoneal morphology over time.

### Study design

This is a multicenter open-labelled, controlled, randomized clinical trial, designed to test the effects of the buffer substance in biocompatible PD fluids on peritoneal small solute transport capacity. All subjects will undergo a 2-month run-in period, in which they receive conventional lactate buffered, acidic, GDP containing PD fluid. During this period, patient eligibility for the trial will be verified and the dialysis dose will be optimized if necessary to ensure appropriate PD adequacy. At the end of this period, the patients will be stratified according to residual renal function (greater or less than 100 ml urine output/day/1.73 m^2^) and the type of phosphate binder therapy (Sevelamer vs. calcium-containing phosphate binders), since these variables may affect the overall efficacy of metabolic acidosis control. Following stratification, subjects will be randomized centrally to receive either the lactate-containing Balance solution or the bicarbonate buffered Bicavera^® ^solution for a period of 10 months. Both during the run-in period and during the intervention phase, patients will be monitored by monthly clinical and laboratory examinations, including capillary blood gas analyses. In addition, peritoneal equilibration tests (PETs), 24-hour dialysate and urine collections and intraabdominal pressure assessments will be performed at time of randomization (with conventional PD fluid) and after 3, 6 and 10 months of treatment (with the study solutions). Also, peritoneal biopsies will be performed on occasion of intraabdominal sugery or laparoscopy prior to start and after termination of the study (usually at time of catheter insertion and renal transplantation).

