### Primary outcome measure

The primary outcome measure will be the longitudinal change in 4h-D/P_creatinine _in the sequential PET examinations. Differential changes in this parameter will indicate differences in the development of the peritoneal solute transport status over time.

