### Sample size estimation

The primary study outcome is the change in 4h-D/P_Cr _from the time of randomization to the conclusion of the 10-month study period. In a previous trial we demonstrated a 6% increase of D/P_Cr _in children on lactate-buffered PD fluid in contrast to a 4% decrease in D/P_Cr _using bicarbonate buffered fluid within 3 months of exposure, resulting in a statistically significant 10% difference in the evolution of peritoneal creatinine transport rate [13]. Assuming that this effect was at least in part due to the different buffer substances applied, a difference in D/P_Cr _at least 7 ± 10% can be expected when Balance and Bicavera^® ^are applied for 10 months. To detect this difference with a sensitivity of 80% and an error probability of 5%, at least 15 patients per randomization group will be required. Assuming a 50% drop-out rate due to renal transplantation and other reasons in the course of the study, 60 patients will have to be enrolled.

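### The change in 4h-D/P creatinine measures the total buffer effect, acute plus chronic, yet the protocol reads it as development of transport status over time

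*Protocol article*

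**What the plan says.** The Study design section has every patient in the run-in on the same fluid: "they receive conventional lactate buffered, acidic, GDP containing PD fluid". It then schedules PETs "at time of randomization (with conventional PD fluid) and after 3, 6 and 10 months of treatment (with the study solutions"). The first test is thus done with a fluid common to both arms. The three later tests are done with Balance (lactate) in one arm and Bicavera (bicarbonate) in the other.

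The Sample size estimation section defines the primary outcome as the change in 4h-D/P creatinine "from the time of randomization to the conclusion of the 10-month study period", so it spans the switch of fluid. The Primary outcome measure section interprets it: "Differential changes in this parameter will indicate differences in the development of the peritoneal solute transport status over time". The hypothesis, in the Objectives of the study section, is that "bicarbonate based PD solutions may allow for a significantly better preservation of peritoneal transport characteristics".

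The Statistical approach section names two analyses: a repeated-measures ANOVA in patients who complete 10 months on study fluid, and a Kaplan-Meier analysis of time to a rise of at least 7.5% in D/P creatinine in all patients started on study fluid.

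The Background reports, from rat intravital microscopy, that "lactate-based neutral-pH PD solution caused mesenteric vasodilation whereas bicarbonate buffered PD fluid had no hemodynamic effects". It also distinguishes "acute or chronic regulation of peritoneal solute transport".

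**The concern.** A PET measures transport while the test fluid is in the abdomen. If lactate raises small-solute transport during the dwell and bicarbonate does not, the arms will differ at months 3, 6 and 10 even when the membranes have evolved identically. The baseline-to-month-10 contrast takes in that offset in full and cannot distinguish it from slow divergence. The protocol's own premise makes this more than a formality: the rat finding concerns the same buffer contrast that is randomized. Its direction, vasodilation with lactate, would be expected to push the result the same way as the trial hypothesis.

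The Kaplan-Meier analysis has a further problem. Each patient is judged against a fixed threshold relative to a test on acidic, GDP-containing fluid. Any immediate response to leaving that fluid shifts the patient towards or away from the threshold at the first study-fluid PET, before any progression.

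At stake is the wording of the conclusion. A difference at month 10 would be a valid effect of buffer on measured transport, but would not by itself show better preservation over time.

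**Working it through.** **Inputs.** Planned difference 7 points and SD 10 (Sample size estimation; the ± value taken as the SD of the change); 15 completers per group and 60 enrolled, so 30 per arm (same section); threshold 7.5% (Statistical approach). The acute effect of buffer on 4h-D/P creatinine is not in the document; a range of 0 to 7 points is assumed.

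**The plan's own figure.** For two groups, two-sided 5% and 80% power, n per arm = 2 × [10 × (1.960 + 0.842) / 7]² = 32.0, or 33 in whole patients; one-sided gives 26. The stated 15 does not reproduce. The drop-out step does: 30 / (1 − 0.5) = 60. That is a separate matter; here only the 7, the 10 and the group sizes are used.

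**What the mean contrast contains.** Let B be the expected baseline value on conventional fluid, A_L and A_B the acute shifts on moving from conventional fluid to the lactate or bicarbonate study fluid, and C_L and C_B the chronic changes by month 10.

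- Expected change, lactate arm: (B + A_L + C_L) − B = A_L + C_L
- Expected change, bicarbonate arm: (B + A_B + C_B) − B = A_B + C_B
- Difference: (A_L − A_B) + (C_L − C_B)

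B drops out under randomization, as does any acute response to pH and GDP that is common to both new fluids. The acute buffer offset a = A_L − A_B stays in full. An a of 3 is 3/7 = 43% of the planned difference; an a of 7 reproduces it with no membrane change. So would 3.5 acute plus 3.5 chronic.

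**Chance of a significant month-10 difference from an acute offset alone** (no chronic difference, SD 10, two-sided 5% t-test):

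| Acute offset (assumed) | 15 per arm | 30 per arm |
|---|---|---|
| 3 | 12.5% | 21% |
| 5 | 26% | 48% |
| 7 | 46% | 76% |

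In 20,000 simulated trials per setting, the month 3-to-10 contrast stayed at about 5% throughout (4.8% to 5.1%), because a constant offset cancels when both tests use the same fluid within an arm.

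**Kaplan-Meier threshold.** With mean change equal to the acute shift s and SD 10, the chance of a rise of at least 7.5 at one PET is 1 − Φ((7.5 − s)/10): 15% for s = −3, 23% for 0, 33% for +3, 40% for +5 and 48% for +7. Here s is A_L or A_B itself, including the part shared by both arms. The document does not give its sign or size.

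**Cost of the month 3-to-10 contrast.** It captures 7/10 of a linear divergence: 0.7 × 7 = 4.9 points. Its SD depends on how the variance of the full change (10² = 100) splits between patient slopes and test error:

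- all slope: 0.7 × 10 = 7
- slope SD 8, error SD 4.24: √[(0.7 × 8)² + 2 × 4.24²] = 8.2
- all error: 10

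The document does not fix the split. Power (two-sided 5%) for 4.9 points at SD 7, 8.2 and 10 is 46%, 35% and 25% at 15 per arm, and 76%, 62% and 46% at 30 per arm. The full change (7 points, SD 10) has 46% and 76%.

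**The case against.** **The objective is broad.** The primary objective is the effect of buffer on transport capacity, the Background lists acute as well as chronic regulation among the open questions, and the Discussion expects vasoactive effects of lactate. A randomized comparison on the fluids patients actually receive answers that objective, acute part included. This stands. A reader might infer that the trial cannot answer its question; the document does not support that. What remains is the narrower inference to preservation and development over time.

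**The baseline cancels.** A reader might also infer that testing on conventional fluid at baseline biases the arm comparison. It does not, on average; the different follow-up fluids create the offset. Only the Kaplan-Meier analysis is exposed to the shared switch.

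**The evidence for an offset is thin.** This largely stands. The Background's human finding of a "slightly lower initial increase of the functional peritoneal surface area during a single PD dwell with pH-neutral compared to acidic solutions" concerns pH, and Table 1 gives pH 7.4 for both study fluids, so it bears on the shared switch and not on the buffer contrast. The buffer evidence is from rats, and no size for D/P creatinine is given.

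**The planned model can already show a step.** True: the data for it will exist, and contrasts are commonly left to an analysis plan, which is not shown. But the protocol itself fixes the endpoint and states its interpretation, and that sentence is what needs correcting.

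**Early divergence may be real.** The Sample size estimation section cites a 10% divergence within 3 months. Reserving the word preservation for the month 3-to-10 contrast would discard a genuine early membrane effect. This stands, and it is why that contrast should be supportive and not a replacement.

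**The second parenthesis in the PET schedule may describe the treatment and not the test fluid.** Possible, but the parallel with the first parenthesis favours the test-fluid reading, and no other test fluid is named.

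**Conclusion.** The point holds as one of interpretation. The randomization-to-month-10 contrast estimates the total buffer effect, and the Primary outcome measure section claims more than that by reading it as development over time. The structure follows from the text, given the test-fluid reading of the PET schedule; the size does not. Over the assumed offsets of 3 to 7 points, with SD 10 and no chronic difference, a significant result would arise with probability 12.5% to 46% at 15 per arm and 21% to 76% at 30 per arm. These figures illustrate sensitivity and do not estimate a bias known to exist. In the Kaplan-Meier analysis, crossings at the first study-fluid PET may reflect the change of fluid, in either direction. A correction is worthwhile and cheap, but the primary outcome itself need not change.

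**What to change.** 1. Keep the baseline-to-month-10 change in 4h-D/P creatinine as the primary outcome and name it the total effect of the buffer, measured on the assigned fluid. Reword the interpretive sentence in the Primary outcome measure section to match.
2. Pre-specify two supportive contrasts from the same repeated-measures model: (a) the between-arm difference at month 3, which is the acute plus early effect; (b) the between-arm difference in change from month 3 to month 10, in which a constant offset cancels.
3. State the reading in advance. Divergence that continues from month 3 to month 10 supports slow membrane change. A step by month 3 followed by parallel courses is reported as an acute or early effect that these data cannot separate, and neither as proof of preservation nor as evidence against it.
4. State with the Kaplan-Meier result that crossings at the first study-fluid PET may reflect the change of fluid.

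The cost is wording and analysis only: no added visits, tests or patients. Contrast (b) generally has less power than the full change (equal only if all the variance is in patient slopes), its 70% share holds only if divergence is linear, it removes only an offset that is constant over time, and it misses chronic change before month 3.

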### Primary outcome measure

The primary outcome measure will be the longitudinal change in 4h-D/P_creatinine _in the sequential PET examinations. Differential changes in this parameter will indicate differences in the development of the peritoneal solute transport status over time.

### Secondary outcome measures

Secondary outcome measures will be surrogate parameters of mesothelial cell viability (CA-125), peritoneal neoangiogenesis (VEGF), fibrotic activity (TGF-β) and local inflammation (IL-6). With the same intention, the evolution of peritoneal histomorphology will be assessed in all patients available for sequential biopsies. Moreover, possible differential effects of lactate and bicarbonate buffer on the control of metabolic acidosis will be assessed by monthly blood gas analyses. Finally, the incidence and clinical course of peritonitis will be recorded as a possible indirect marker of local peritoneal macrophage function.

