### Statistical approach

A computer based randomization protocol will be generated and applied centrally at the end of the run-in period. Baseline comparability between the two treatment groups will be evaluated with respect to entry criteria. Chi-square and t-tests will be used to assess differences between the two groups on the baseline variables. Any variables that are found to be discrepant between the two groups and that are related to the outcome variables will be treated as co-variates in later analyses.

In order to evaluate the patients' change in D/P_Cr _ratios, two strategies will be employed:

1. Repeated measure ANOVA will be performed on those patients who complete the 10-month observation period on the study medications.

2. The Kaplan-Meier method will be used to estimate the time in which patients are likely to display a ≥ 7.5 % increase in the D/P_Crea _ratio during the 10-month period. All patients started on study medication will be available for this analytical approach.

The same strategies will be used to analyze secondary outcome variables.

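### Monthly acidosis data are assigned a completer repeated-measures ANOVA with only conditional baseline adjustment; a baseline-adjusted mean of the on-treatment months would be clearly more efficient for a sustained buffer effect.

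*Protocol article*

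**What the plan says.** The Study design section states that, in run-in and treatment alike, "patients will be monitored by monthly clinical and laboratory examinations, including capillary blood gas analyses". Treatment lasts 10 months. The Secondary outcome measures section turns those samples into an outcome: "control of metabolic acidosis will be assessed by monthly blood gas analyses".

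The Statistical approach section gives two strategies for D/P creatinine. The first is: "Repeated measure ANOVA will be performed on those patients who complete the 10-month observation period on the study medications". The second is a Kaplan-Meier analysis of the time to a rise of at least 7.5% in D/P creatinine, for which "All patients started on study medication will be available for this analytical approach". It then adds: "The same strategies will be used to analyze secondary outcome variables". Baseline variables become covariates only if they differ between the arms and are related to outcome.

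The article gives no SD, correlation, effect size or power for blood bicarbonate. It does not say which ANOVA effect (group or group-by-time) is the test for acidosis, or whether a sphericity correction will be applied.

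**The concern.** A method written for four peritoneal equilibration tests is carried over to a series of about 11 monthly values. Three features cost efficiency.

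- **Group-by-time test.** It spreads a sustained difference over ten contrasts. Without correction it also relies on sphericity, which fails when neighbouring months are more alike than distant ones.
- **Group main effect.** If the randomisation value is included, this effect averages in a measurement taken before the fluids differ. In any case it does not use that value as a predictor.
- **Completer restriction.** It drops children who leave early, although their monthly values up to that point are collected and the protocol expects 50% drop-out.

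Acid-base status is the first-named secondary objective, and both stratification factors were chosen because they may affect acidosis control. The stake is a real buffer difference that goes undetected although the data collected could show it.

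**Working it through.** **Plan's own figure.** There is none for acidosis. The only design figure is for D/P creatinine: "at least 15 patients per randomization group will be required". Two arms of 15 make 30 completers, and 30/(1 − 0.5) = 60 enrolled, as stated. I take 15 per arm as given; whether it suffices for the primary outcome is a separate question.

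**Inputs from the article.** n = 15 completers per arm. Values at randomisation and months 1 to 10 make 11, so the group-by-time test has (2 − 1)(11 − 1) = 10 numerator degrees of freedom.

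**Assumed inputs.** Variance of a single value = 1, split into 0.4 between children and 0.6 within. The within part is serial (AR(1), monthly correlation 0.7 or 0.9), white noise, or a mixture. The effect is 0.8 SD, constant from month 1. Alpha is 5%, two-sided.

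**Formulas.** Let V be the variance of a child's mean over months 1 to 10, and c its covariance with the randomisation value. The arm difference has

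- unadjusted: SE = √(2V/15)
- ANCOVA: SE = √(2(V − c²)/15), because the randomisation value has variance 1
- group main effect over 11 values: effect 0.8 × 10/11 = 0.727, with V₁₁ in place of V.

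*Within-child variation all noise.* V = 0.4 + 0.6/10 = 0.46, c = 0.4, V − c² = 0.46 − 0.16 = 0.30, V₁₁ = 0.4 + 0.6/11 = 0.455.

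- ANCOVA: 0.8/√(2 × 0.30/15) = 0.8/0.200 = 4.00, power 97%
- Unadjusted mean: 0.8/√(2 × 0.46/15) = 0.8/0.248 = 3.23, power 88%
- Main effect: 0.727/√(2 × 0.455/15) = 0.727/0.246 = 2.95, power 81%

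*Within-child variation fully serial, correlation 0.9.* The mean of 0.9¹ to 0.9¹⁰ is 0.586, so c = 0.4 + 0.6 × 0.586 = 0.752. Summing the covariance matrix gives V = 0.837 and V₁₁ = 0.824; V − c² = 0.271.

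- ANCOVA: 0.8/√(2 × 0.271/15) = 0.8/0.190 = 4.2, power 98%
- Unadjusted mean: 0.8/√(2 × 0.837/15) = 0.8/0.334 = 2.4, power 64%
- Main effect: 0.727/√(2 × 0.824/15) = 0.727/0.331 = 2.2, power 56%

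**Simulation over all assumed structures** (4,000 trials per setting):

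| Analysis | Power, sustained 0.8 SD |
|---|---|
| Group-by-time, Greenhouse-Geisser corrected | 30–58% |
| Group main effect, randomisation value included | 57–81% |
| Group effect over months 1 to 10 only | 64–88% |
| ANCOVA on mean of months 1 to 10, adjusted for end-of-run-in value | 94–98% |

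**False positives.** ANCOVA holds about 5%, and so does the group main effect (4.4–5.8%). An uncorrected group-by-time test runs at about 4–8% with noise or mixed variation, and at 9–13% when within-child variation is fully serial. With the four PET visits (months 0, 3, 6, 10) the same uncorrected test stays at 4.9–6.6% for AR(1) correlation 0.5 to 0.95, so the exposure comes from the longer series.

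**Other effect shape.** If the effect grows linearly and ANCOVA power is set near 80%, the corrected interaction has 33–79% against 78–79% for ANCOVA. At a between-child share of 0.4 with serial correlation 0.7, it is 70% against 78%.

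**The case against.** A reader might infer that the article prescribes an uncorrected group-by-time F test, and hence a false-positive rate of about 12% and half the power of a mean-of-months comparison. The documents do not support that.

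- **Test not named.** The article names repeated-measures ANOVA but not the effect to be read for acidosis. Its language of differential change belongs to D/P creatinine, and control of acidosis can equally be read as a question of level.
- **Correction not excluded.** The choice of effect and of sphericity correction is commonly left to an analysis plan, which is not shown. A Greenhouse-Geisser correction is compatible with the text as written.
- **Same method, other effect.** Over months 1 to 10 the ANOVA group effect is exactly the unadjusted mean-of-months comparison. Much of the gap to 94–98% therefore comes from baseline adjustment, not from averaging.
- **Worst case only.** Rates of 9–13% need within-child variation with no noise, which is unlikely for single capillary samples. Nor is 13% a ceiling: pure AR(1) at 0.95 to 0.99 gives 13–14%, and compound symmetry gives 5.0%.
- **Effect shape.** A constant shift is not assured, since dialysis dose is individually tailored and bicarbonate supplements may be re-instituted.

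All of this stands and limits the point to efficiency. Two further replies do not remove it. The covariate rule does not supply the adjustment: it acts only when the arms look different, whereas the precision gain comes from the correlation between baseline and later values. If discrepant means significant at 5%, randomisation alone makes baseline bicarbonate discrepant in about 1 trial in 20. The Kaplan-Meier strategy does include all treated children, but its only stated threshold is for D/P creatinine, and dichotomising bicarbonate would discard information.

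**Conclusion.** The point holds as one of efficiency in a stated analysis, and the improvement is cheap. It is not an error or a contradiction. For a sustained 0.8 SD shift with 15 per arm, ANCOVA on the on-treatment mean has about 94–98% power, against 57–81% for the group main effect (64–88% over months 1 to 10 only) and 30–58% for the corrected interaction. These figures rest on an assumed variance split, serial correlation and effect shape, none of which the article gives. For a growing effect the advantage over the corrected interaction shrinks or disappears. Inflated false positives would arise only if group-by-time were tested without correction, which the article does not say; the group main effect is not inflated. The figures compare analyses at equal numbers, so any gain from including children who leave early is not counted in them.

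**What to change.** In the Statistical approach section, add a separate statement for acid-base status:

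- Compare blood bicarbonate between arms by ANCOVA on each child's mean over the available on-treatment months, adjusted for the end-of-run-in value whether or not the arms differ at baseline.
- Show monthly means by arm descriptively.
- For any month-by-month test, use a sphericity correction or an unstructured covariance.

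The cost is wording only, since every value is already collected. One averaged contrast does not test the shape of the time course and loses some sensitivity to a late-developing effect. Means from children who leave early rest on fewer and earlier months. The monthly display keeps the time course visible.
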